### Treatment fidelity

To ensure consistency, interventions will be administered by licensed acupuncturists with at least three years of clinical experience. In the event of absence, a trained substitute will ensure continuity. Acupuncturists are independent of the research team and blinded to study objectives. Prior to trial initiation, they will complete intensive training workshops on the standardized protocol, including acupoint location, procedural steps, and safety precautions. Training will include demonstrations, role-play, and feedback sessions.

Acupuncturists will be provided with detailed manuals specifying acupoint selection, device application, and treatment timing. Treatment fidelity will be monitored through random review of 15% of recorded sessions by an independent panel of experienced acupuncturists, stratified across providers and intervention stages (early, mid, late). Assessments will follow the revised Standards for Reporting Interventions in Clinical Trials of Acupuncture (STRICTA) guidelines (40), focusing on: (1) accuracy of acupoint location; (2) consistency in timing and session length; (3) adherence to standardized procedures; and (4) inter-rater reliability, measured by Cohen’s Kappa coefficient.

In cases of protocol deviations, the principal investigator will conduct feedback sessions with the involved acupuncturist, provide corrective recommendations, and oversee follow-up monitoring to confirm compliance. Ongoing support will be provided to maintain procedural consistency throughout the trial.

## Outcomes

### Primary outcome

Quality of sleep. The primary outcome is global sleep quality assessed by the PSQI, a 19-item questionnaire widely used to evaluate sleep quality and disturbances over the past month (41). The PSQI includes 4 open-ended and several closed-ended items scored on a 4-point Likert scale, covering subjective sleep quality, sleep latency, sleep duration, sleep efficiency (SE), sleep disturbances, sleep medication use, and daytime dysfunction. The total score ranges from 0 to 21, with higher scores indicating poorer sleep quality and more severe disturbances. A cutoff point of more than 5 is considered as having significant disturbance in sleep quality, which demonstrates a sensitivity of 90% and specificity of 87% (41). The Chinese version of the PSQI has been validated among Chinese medical students, showing acceptable internal consistency (Cronbach’s α = 0.734) (42).

### Secondary outcomes

Insomnia severity. Insomnia severity will be assessed using the Insomnia Severity Index (ISI) (43), a seven-item scale rated from 0 (no problem) to 4 (very severe), with total scores ranging from 0 to 28. Higher scores indicate greater severity: 0–7 = no clinically significant insomnia, 8–14 = subthreshold, 15–21 = moderate, and 22–28 = severe. The Chinese version has shown good reliability in hospital patients (Cronbach’s α = 0.804) (44).

Depression severity. Depressive symptoms will be assessed with the 17-item Hamilton Depression Rating Scale (HAMD-17) (45). Each item is scored on a 3- or 5-point scale, with higher totals indicating greater severity. The Chinese version has demonstrated good reliability (Cronbach’s α = 0.798–0.810) in patients with depression (44). Administration will be performed by an experienced psychiatrist from the Second Affiliated Hospital of XXMU, who is independent of the study team and blinded to study objectives.

Biomarkers. Serum biomarkers will be collected at baseline, post-treatment, and follow-up (08:00 a.m., fasting samples). Levels of 5-HT and CORT, key regulators of sleep and mood, will be quantified using enzyme-linked immunosorbent assay (ELISA) (46, 47).

Actigraphy. Objective sleep parameters will be measured using the ActiGraph wGT3X-BT (ActiGraph LLC, Pensacola, FL, USA), a validated device widely applied in sleep research. Participants will wear the actigraph on the non-dominant wrist for seven consecutive nights, removing it only when necessary to avoid water damage. Data will be collected at 30 Hz and analyzed in 60-second epochs using ActiLife software (version X.X). Sleep–wake scoring will follow the Sadeh algorithm, providing indices such as sleep onset latency, total sleep time, wake after sleep onset, sleep efficiency, nocturnal awakenings, and binary sleep–wake status.

Drug dose record. Participants will complete a daily medication diary from baseline through the 12-week follow-up, documenting drug name, dosage, and exact administration time.

Participant compliance. Adherence to the intervention will be systematically monitored. Reasons for non-compliance (e.g., absences, withdrawal, loss to follow-up, decreased engagement, aversion to treatment, or physical discomfort) will be documented to preserve study rigor.

AEs. AEs will be monitored and classified by severity (mild, moderate, severe). Mild events will be observed; moderate events will trigger timely clinical management; severe events will result in treatment discontinuation and referral to appropriate care. Incidence will be summarized by group, and serious AEs will be followed until resolution.

### Blinding assessment

At the end of the treatment phase, an independent assessor will ask participants in the two intervention groups (LA and SLA) to indicate their perceived allocation by choosing one of three options: LA, SLA, or “I do not know.” Each response will be documented, and the results will be analyzed to evaluate the success of blinding.

The Bang Blinding Index (BBI) will be calculated separately for each intervention group as:

$$BBI_{i}=p_{correct,i}-p_{incorrect,i},i\in \{1,2\}$$

where *p_correct,i_* and *p_incorrect,i _*are the proportions of correct and incorrect guesses in group *i*. “I don’t know” responses are counted in the denominator but not in the numerator. A BBI value between –0.20 and +0.20 will be considered evidence of adequate blinding, whereas values approaching +1 indicate unblinding (48).

### Safety evaluation

Safety will be evaluated throughout the study to ensure participant well-being and to identify potential risks associated with LA, SLA, and control conditions. AEs are defined as any unfavorable or unintended medical occurrence during participation, regardless of its causal relationship to the intervention.

All AEs will be recorded in the CRF, with details on onset, duration, management, and outcome. The investigator will also assess causality, determining whether each AE is related to the intervention. SAEs—such as hospitalization, life-threatening complications, or worsening psychiatric symptoms—will be reported to the ethics committees within 24 hours and followed until resolution or stabilization.

Incidence of AEs will be summarized across groups, and dropout rates due to AEs will be monitored as part of the safety analysis. Participants will receive emergency contact information to report symptoms at any time during the trial. This monitoring framework ensures transparent reporting and timely management of safety concerns.

### Sample size calculation

Sample size estimation was performed using G*Power version 3.1.9.2 (Heinrich Heine University, Düsseldorf, Germany) (49). The calculation was based on a repeated-measures, between–within interaction analysis of variance (ANOVA) with the changes in PSQI across time as the primary outcome. An effect size of f = 0.158 was adopted from a RCT investigating LA in patients with co morbid insomnia, depression and anxiety (50). This effect size was chosen as a conservative estimate, reflecting clinically meaningful but mild improvements in sleep quality. Parameters were set at a two-tailed significance level (α) of 0.05, statistical power (1–β) of 0.80, number of groups = 3 and number of measurements = 3. Under these conditions, the minimum required sample size was calculated to be 84 participants across three arms. To account for an anticipated dropout or attrition rate of approximately 30%, the final adjusted sample size was set at 108 participants, with 36 subjects per group (LA, SLA, and control). This sample size is expected to provide sufficient power to detect between-group differences and to remain robust against missing data or attrition.

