## Methods

### Study design

This is a three-year, single-center, randomized, single-blind, three-arm parallel randomized controlled trial (RCT) conducted at The Second Affiliated Hospital, Xinxiang Medical University (XXMU), China. Ethical approval was obtained from the Ethics Committees of XXMU (XYEFYLL-(Research)-2024-36) and Universiti Sains Malaysia (USM) (USM/JEPeM/PP/24070605). The trial is registered at ClinicalTrials.gov (NCT06443242) and follows Consolidated Standards of Reporting Trials (CONSORT) guidelines.

A total of 120 inpatients with major depressive disorder (MDD) and comorbid insomnia will be randomized (1:1:1) to one of three groups: laser acupuncture (LA)—low-dose laser therapy delivered at acupoints; sham laser acupuncture (SLA)—identical procedures without effective laser output; or standard care.

The intervention will last 6 weeks with a 12-week follow-up. The primary outcome is sleeping quality (PSQI), while secondary outcomes include depressive symptoms and serum biomarkers (5-HT, CORT). AEs will be monitored and reported to both ethics committees. **Figure 1** provides a flowchart outlining the study procedures and outcome measures. The CONSORT checklist for this RCT is presented in **Supplementary Material 1**, while the CONSORT flow diagram for participant enrolment, allocation, follow up and analysis is presented in **Supplementary Material 2**.

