### Randomization, allocation concealment and blinding

Stratified permuted block randomization will be applied to assign participants to the LA, SLA, and control groups in a 1:1:1 ratio. Stratification will be based on age (18–40 vs. 41–60 years) and gender (male vs. female), resulting in four strata: (1) males aged 18–40 years, (2) males aged 41–60 years, (3) females aged 18–40 years, and (4) females aged 41–60 years. Within each stratum, randomization sequences will be generated using permuted blocks to ensure balance until a total of 40 participants per group are enrolled (120 in total).

The randomization sequence will be generated by an independent research assistant who is not involved in the study, using GraphPad QuickCalcs, a validated web-based program for generating block randomization schemes. Allocation codes will be sealed in sequentially numbered opaque envelopes prepared by independent personnel. At enrolment, envelopes will be opened in sequence by study staff according to the order of patient visits, ensuring allocation concealment. Participants will be informed that they have an equal probability of assignment to each of the three groups.

This study will be conducted as a single-blind trial. Participants, outcome assessors, data collectors, and statisticians will remain blinded to group allocation, while acupuncturists delivering the interventions cannot be blinded due to the nature of the procedures. To maintain blinding integrity, acupuncturists will strictly follow a standardized intervention manual to minimize performance bias.

During treatment, participants will receive therapy in a closed room and will be required to wear blindfolds to prevent observation of laser irradiation. Communication among participants will be restricted, and scheduling will minimize cross-interaction. Researchers will not access unblinded data until data collection and statistical analysis are complete. Allocation concealment and restricted data access will further reduce the risk of bias, thereby strengthening the methodological rigor of the trial.

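### The sample-size section gives 108 patients (36 per group) for 84 evaluable and 30% attrition; its own inputs give 120, the number stated everywhere else

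*Protocol article*

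**What the plan says.** The Sample size calculation section of the protocol article sizes the trial with a "repeated-measures, between–within interaction analysis of variance (ANOVA") on PSQI over time. It uses f = 0.158, α of 0.05 (two-tailed), power of 0.80, three groups and three measurements, and arrives at a minimum of 84 participants. It then allows for losses of about 30% and gives the size it reaches in these words: "the final adjusted sample size was set at 108 participants, with 36 subjects per group (LA, SLA, and control"). The section goes on to claim that this size is robust to attrition.

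Three other places give a different size. The Abstract (Methods) has 120 inpatients randomized 1:1:1. Study design says the same: "A total of 120 inpatients with major depressive disorder (MDD) and comorbid insomnia will be randomized (1:1:1"). The section on randomization, allocation concealment and blinding makes it the rule for the allocation sequences, which run "until a total of 40 participants per group are enrolled (120 in total"). The figure 108 appears only in the sample-size section, and nothing describes it as a subset of the 120, such as an evaluable set or a lower limit.

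**The concern.** There are two linked problems. First, the document states two final sizes, 108 and 120, and does not reconcile them. Second, 108 does not follow from the section's own inputs: an allowance for 30% loss on 84 evaluable participants needs more than 108.

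The number fixes when recruitment ends and how long the randomization lists must be. A team that closes at 36 per group would satisfy the sample-size section, breach the randomization section, and fall short of the planned power at the attrition the protocol itself expects. A team that goes to 40 per group would have an adequate trial, but the stated result of its sample-size calculation would not be the size it used.

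**Working it through.** **Inputs, all from the Sample size calculation section:** f = 0.158; α = 0.05; power 0.80; k = 3 groups; m = 3 measurements; evaluable N = 84; attrition about 30%; stated final N = 108. The correlation between repeated measures (ρ) and the non-sphericity correction (ε) are not stated, so they are assumptions here.

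**Step 1: reproduce the 84.** The G*Power formula for the within-between interaction uses a non-central F distribution with

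- λ = f² · N · m · ε / (1 − ρ)
- df1 = (k − 1)(m − 1)ε
- df2 = (N − k)(m − 1)ε

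With ρ = 0.5, ε = 1 and N = 84: λ = 0.024964 × 84 × 3 / 0.5 = 12.58, df1 = 4, df2 = 162, power 0.8105. At N = 81 power is 0.794. The smallest balanced N that reaches 0.80 is therefore 84, as the protocol states. Over a grid of ρ from 0.3 to 0.7 in steps of 0.1 and ε of 0.5, 0.75 and 1, only ρ = 0.5 with ε = 1 returned 84.

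**Step 2: adjust for attrition.** The number to randomize is N / (1 − d):

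- 84 / (1 − 0.30) = 120, which is 40 per group.
- This does not reproduce 108; 120 is 11% higher (120/108 = 1.11).
- Multiplying instead of dividing gives 84 × 1.30 = 109.2, or 28 × 1.30 = 36.4 per group. Rounded down to 36 per group, that is 108, and it probably explains the printed figure. Multiplying by 1.30 is not the right adjustment, since 30% is then lost from the enlarged number.

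**Step 3: what each size delivers.**

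| Randomized | Completers at 30% loss | Attrition that still leaves 84 | Power on completers (ρ = 0.5, ε = 1) |
|---|---|---|---|
| 108 | 108 × 0.70 = 75.6 | 1 − 84/108 = 22.2% | 0.757 at 75; 0.763 at 76 |
| 120 | 120 × 0.70 = 84 | 1 − 84/120 = 30% | 0.81 |

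**Step 4: sensitivity to the unstated correlation.** With 75 completers and ε = 1:

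| ρ | Balanced N required | Power at 75 |
|---|---|---|
| 0.48 | 87 | 0.74 |
| 0.50 | 84 | 0.76 |
| 0.52 | 81 | 0.78 |
| 0.55 | 75 | 0.81 |

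Power at 75 passes 0.80 only at a correlation for which the protocol's own requirement would have been 75, not 84.

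**The case against.** The strongest reply is that 120 is the operative number. The randomization section fixes the length of the lists at 40 per group, and the Abstract and Study design agree. With 120 randomized and 30% lost, exactly 84 remain, so no power is lost. The inputs printed in the sample-size section also support 120; only the printed result does not. This stands, and it makes the power loss conditional on 108 being followed. It does not remove the contradiction, because the sample-size section calls 108 the final adjusted size.

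A second reply is that 108 has an explanation: 28 × 1.3 = 36.4, rounded down to 36 per group, with attrition given only as approximate. That is probably how the figure arose, but the method is wrong, and an approximate 30% does not stretch to the 22% that 108 covers.

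A third reply is that about 75 completers is not necessarily the number analysed. The Statistical methods section plans an intention-to-treat analysis, and the Missing data section applies multiple imputation when 5% to 40% of data are missing. Patients lost after the 6-week visit would still contribute a post-treatment value. So the power of about 0.76 may understate what 108 would give. But the section sized the trial by inflating for dropout, and on that basis 108 falls short.

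Last, the power figures rest on a correlation and a sphericity value that the protocol does not give. That is so; the comparisons of 108 with 120, and of 75.6 with 84, need neither.

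**Conclusion.** The concern holds. The final size in the sample-size section is wrong on its own inputs and contradicts three other places: it should be 120 (40 per group), not 108 (36 per group), a difference of 12 patients, or 4 per group. This part rests only on figures printed in the protocol.

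The effect on power is conditional. If 108 were randomized and 30% lost, the 75 or so completers would give power of about 0.76, roughly 4 points below the stated 0.80 (0.74 to 0.78 for a correlation of 0.48 to 0.52). That assumes sphericity and an analysis of completers. If 120 are randomized, the planned power is kept and what remains is an error in the justification. Because the figure governs when recruitment stops, it must be corrected.

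**What to change.** In the Sample size calculation section, replace 108 participants and 36 per group with 120 participants and 40 per group, and show the step 84 / (1 − 0.30) = 120. The section then agrees with the Abstract, Study design and the randomization section. This costs one sentence and no extra patients.

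If 108 was really intended, the Abstract, Study design and the randomization section must all change to 108 (36 per group). The sample-size section must then either restate the attrition covered as about 22%, or state that power on completers is about 76% at 30% attrition, with the assumed correlation and sphericity named.

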### Statistical methods

All analyses will be conducted using statistical package for the social sciences (SPSS) version 28.0 (IBM Corp., Armonk, NY, USA) (51). Continuous variables will be summarized as mean ± standard deviation (SD) for normally distributed data, or as median (interquartile range, IQR) for non-normally distributed data. Categorical variables will be expressed as frequencies and percentages. A two-tailed p value < 0.05 will be considered statistically significant.

Primary outcomes. Changes in PSQI scores, sleep efficiency, total sleep time, and number of awakenings will be analyzed using a mixed-design ANOVA (52), with intervention group (LA, SLA, control) as the between-subject factor and time (baseline, post-treatment, follow-up) as the within-subject factor. Standardized mean differences will be calculated as effect sizes. Significant interactions will be followed by *post-hoc* pairwise comparisons. All primary analyses will follow the intention-to-treat (ITT) principle, with participants analyzed according to initial randomization regardless of adherence or withdrawal.

Secondary outcomes. ISI, HAMD-17, and biomarker levels (CORT, 5-HT) will be analyzed as continuous variables using mixed ANOVA across three time points. Actigraphy-derived sleep parameters will be analyzed similarly. Dropout rates due to AEs will be compared among groups using Pearson’s χ² test or Fisher’s exact test, as appropriate.

A subgroup analysis will be performed in which participants treated with LA will be subdivided into those on selective serotonin reuptake inhibitor (SSRI), serotonin noradrenaline reuptake inhibitor (SNRI) and other antidepressants and on low to moderate dose (less than optimal dose of antidepressant) and on high dose (above the optimal dose of antidepressant) using generalized estimated equation (GEE) where the dependent variable is dummy coded as 0 = without sleep quality disturbance (PSQI ≤ 5) and 1 = with sleep quality disturbance (PSQI > 5).

Sensitivity analysis. A per-protocol analysis will be conducted using the same statistical tests, excluding participants who fail to complete at least 5 of the 6 weekly intervention sessions. Findings will be compared with ITT results.

Missing data. If <5% of data are missing, they will be ignored under the assumption of missing completely at random. When missingness is between 5% and 40%, multiple imputation using chained equations will be applied (Stata 15.0, StataCorp, College Station, TX, USA) (53). If >40% of data are missing or suspected to be non-random, available data will be analyzed with explicit acknowledgment of this limitation.

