**Methods:**

A total of 120 inpatients meeting all eligibility criteria will be randomized (1:1:1) to LA, SLA, or control. The primary outcome is the Pittsburgh Sleep Quality Index (PSQI). Secondary outcomes include the Insomnia Severity Index (ISI), the 17-item Hamilton Depression Rating Scale (HAMD-17), serum 5-hydroxytryptamine (5-HT) and cortisol (CORT), and actigraphy. Outcomes are assessed at t0, t1, and t2. Safety will be evaluated by adverse events (AEs) and discontinuations due to adverse effects. Analyses will follow the intention-to-treat principle.

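### The statistical section lists four primary outcomes where the rest of the protocol names PSQI alone

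*Protocol article*

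**What the plan says.** The protocol article identifies the primary outcome in five places.

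- **Abstract (Methods):** PSQI is the primary outcome. Actigraphy is secondary: "Secondary outcomes include the Insomnia Severity Index (ISI), the 17-item Hamilton Depression Rating Scale (HAMD-17), serum 5-hydroxytryptamine (5-HT) and cortisol (CORT), and actigraphy".
- **Study design:** PSQI is the primary outcome. Depressive symptoms and serum biomarkers are given as secondary. Actigraphy is not mentioned here.
- **Primary outcome:** "The primary outcome is global sleep quality assessed by the PSQI".
- **Sample size calculation:** the calculation is built on one outcome, "with the changes in PSQI across time as the primary outcome", with alpha 0.05 and power 0.80.
- **Statistical methods:** "Primary outcomes. Changes in PSQI scores, sleep efficiency, total sleep time, and number of awakenings will be analyzed using a mixed-design ANOVA".

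Two more places bear on the three added variables. The *Secondary outcomes* section defines total sleep time, sleep efficiency and nocturnal awakenings among the actigraphy indices. The secondary-outcome paragraph of *Statistical methods* then says "Actigraphy-derived sleep parameters will be analyzed similarly".

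The only significance criterion is a general one at the start of *Statistical methods*: "A two-tailed p value < 0.05 will be considered statistically significant".

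**The concern.** Four places agree on a single primary outcome. The paragraph that specifies its analysis names four. A reader who works only from the statistical section would conclude that a significant group-by-time result for awakenings is a primary result of the trial. A reader of any other section would call it secondary.

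Two things are at stake. The first is which result decides the trial, since a null PSQI with a positive result on one of the other three would be described differently depending on the section consulted. The second is the meaning of the 0.05 level: the sample size spends all of it on PSQI, and nothing in the statistical paragraph says how the other three variables relate to it.

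**Working it through.** **1. Side by side.**

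| Place in the protocol article | Primary | Status of the other three |
|---|---|---|
| Abstract | PSQI | actigraphy secondary |
| Study design | PSQI | not mentioned |
| Primary / Secondary outcomes | PSQI global score | defined as actigraphy indices, secondary |
| Sample size calculation | PSQI | not mentioned |
| Statistical methods, primary paragraph | PSQI and three more | primary, source not stated |
| Statistical methods, secondary paragraph | – | actigraphy parameters secondary |

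The names in the primary paragraph match the actigraphy indices closely, so actigraphy is the likelier source. It is not certain: the *Primary outcome* section also lists sleep efficiency and sleep duration as PSQI components.

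**2. The plan's own sample size.** Stated inputs: f = 0.158, alpha 0.05, power 0.80, 3 groups, 3 measurements, result 84. Assumed, because the article does not give them: correlation between repeated measures 0.5 and sphericity factor 1. For the within-between interaction:

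- noncentrality = f² × N × m / (1 − rho) = 0.158² × 84 × 3 / 0.5 = 12.58
- df1 = (3 − 1)(3 − 1) = 4; df2 = (84 − 3)(3 − 1) = 162
- power at N = 84 is 81.0%; at N = 81 it is 79.4%

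The stated 84 is therefore reproduced in multiples of 3. It depends on the assumed correlation: the same calculation gives 99 at rho = 0.4 and 69 at rho = 0.6. It is the size for **one** outcome tested at the full 0.05.

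**3. False-positive rate under each possible reading.**

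- *PSQI alone decides:* 5%.
- *All four must be significant:* not inflated, at most 5%, but power falls.
- *Any one of four is enough, independent outcomes:* 1 − 0.95⁴ = 1 − 0.8145 = 18.5%. The bound under any dependence is 4 × 0.05 = 20%.
- *Any one of four is enough, correlated outcomes:* the correlations are not given, so a range was simulated (null interaction F tests, N = 84, equal correlation between outcomes, 20,000 runs each).

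| Assumed correlation | Chance of at least one p < 0.05 |
|---|---|
| 0 | 18.1% |
| 0.3 | 17.4% |
| 0.5 | 16.5% |
| 0.7 | 13.8% |
| 0.9 | 9.9% |

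The simulated 18.1% agrees with the exact 18.5% within simulation error (standard error √(0.18 × 0.82 / 20,000) = 0.27 percentage points).

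**4. What four genuine primaries would need.** With an any-one rule, a Bonferroni level of 0.05 / 4 = 0.0125 and, as an assumption, the same f for each outcome, power per outcome at 84 evaluable participants is 63.2%, and 111 evaluable would be needed for 80%. With the plan's 30% attrition that is 111 / 0.70 = 158.6, so 159 randomised. The stated sample size fits a single primary outcome.

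**The case against.** The best defence is that PSQI is plainly the primary outcome: four places say so, the sample size rests on it, and one paragraph is loosely drafted. That is probably what happened, and much of the defence stands. It rules out several stronger readings.

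- A reader might infer that success is undefined throughout the protocol. It is not. Every section except the statistical one points to PSQI, and only the statistical section is out of line.
- A reader might infer that type I error *is* 18.5%. No passage says that one significant result out of four is enough. The p < 0.05 sentence is a general threshold for all analyses and does not serve as a success rule. The 18.5% also needs independence, which is unlikely among sleep measures.
- A reader might infer that the deciding outcome could be chosen after the data are seen. The trial is registered, and the article commits to updating the registry if outcome measures change. The registry record is not available here, so this cannot be established.
- The lack of a named multiplicity procedure carries no weight by itself, since an analysis plan that is not shown may contain one.
- That the three variables come from actigraphy is an inference from their names.

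The contradiction survives all of this. It is not detail lost in condensing: the article states the primary outcome in two incompatible ways, and any analysis plan would have to depart from one of them. If the paragraph is a drafting slip, that is a reason to correct it.

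**Conclusion.** The point holds as a contradiction in the text. The primary paragraph of *Statistical methods* names four outcomes where the abstract, *Study design*, *Primary outcome* and *Sample size calculation* name one, and three of the four appear elsewhere as secondary. It should be settled before any data are seen, because it determines which result decides the trial.

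The numerical consequence depends on a rule that the article does not state. It is 5% if PSQI alone decides, and about 10% to 18.5% if any one of the four is enough, for assumed between-outcome correlations from 0.9 down to independence. The overlap between primary and secondary measures is likely from the names but unconfirmed, because the paragraph does not give the source of the three variables.

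**What to change.** In *Statistical methods*, make the heading of the primary paragraph singular and keep only the PSQI global score in it. Move sleep efficiency, total sleep time and number of awakenings to the secondary-outcome paragraph, label them supportive with no claim of trial success, and state whether each comes from actigraphy or from PSQI items.

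The cost is wording in one paragraph. No visit, measurement or test changes, and the sample-size basis of one outcome at alpha 0.05 stays as it is. The sponsor gives up three extra results that could have been called primary.

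### The primary mixed-design ANOVA treats baseline PSQI as an outcome level instead of adjusting for it: valid, but it forgoes precision worth about 25% of the variance of a pairwise contrast if the correlation is 0.5 and the SDs are equal

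*Protocol article*

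**What the plan says.** Under Statistical methods, Primary outcomes, the protocol article states: "Changes in PSQI scores, sleep efficiency, total sleep time, and number of awakenings will be analyzed using a mixed-design ANOVA". The factors are then fixed, "with intervention group (LA, SLA, control) as the between-subject factor and time (baseline, post-treatment, follow-up) as the within-subject factor", and the pairwise comparisons depend on the interaction test: "Significant interactions will be followed by" post-hoc comparisons. No covariate is named. The same type of model is set for ISI, HAMD-17, cortisol, 5-HT and actigraphy.

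The abstract confirms that a baseline value exists for every patient: "Outcomes are assessed at t0, t1, and t2". The randomisation section states: "Stratification will be based on age (18–40 vs. 41–60 years) and gender (male vs. female), resulting in four strata". Neither stratification factor appears in the stated model. The Sample size calculation section rests on the same interaction test: "The calculation was based on a repeated-measures, between–within interaction analysis of variance (ANOVA) with the changes in PSQI across time as the primary outcome". It gives no correlation between visits and no SD.

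**The concern.** When baseline is a level of the time factor, the group-by-time contrast for t1 or t2 against baseline is a difference between arms in mean change. In a randomised trial the arms share the same expected baseline, so the baseline value can be used as a covariate instead. Regression then chooses the best weight for baseline, whereas a change score forces that weight to be 1. Any other best weight means that the change score carries avoidable noise.

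What is at stake is precision. The comparison that isolates the laser itself, LA against SLA, has at most 40 patients per arm, and the minimum of 84 corresponds to 28 per arm. Wider intervals than the data require matter at that size. A chance imbalance in baseline PSQI is also handled less well by a change score than by regression adjustment.

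**Working it through.** **Inputs from the protocol article.** Three groups, three measurements, α = 0.05, power 0.80, f = 0.158, minimum N = 84 (Sample size calculation). Strata: age 18–40 or 41–60, and gender (Randomization section). The correlation ρ and the SDs are not stated.

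**1. Reproducing N = 84.** For the within-between interaction, λ = f²·N·m/(1−ρ), df1 = (k−1)(m−1) = 4 and df2 = (N−k)(m−1), with k = m = 3 and sphericity. At N = 84 and ρ = 0.5, λ = 0.158² × 84 × 3 / 0.5 = 12.58, df2 = 162 and power is 0.81. At N = 81 power is 0.794, so 84 is the smallest N with equal arms. Other correlations give other totals: 114 at ρ = 0.3, 99 at 0.4, 69 at 0.6 and 51 at 0.7. The stated 84 therefore implies ρ = 0.5 as the planning input.

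**2. The two variances.** Let s0 and s1 be the SDs at baseline and at one later visit. Apart from the common factor 2/n for a pairwise contrast:

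- change score: s0² + s1² − 2ρ·s0·s1
- baseline-adjusted: s1²(1−ρ²)
- difference: s0² − 2ρ·s0·s1 + ρ²·s1² = (s0 − ρ·s1)²

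The difference cannot be negative. It is zero only when s0 = ρ·s1.

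**3. Equal SDs (assumption).** With s0 = s1 = 1 the variances are 2(1−ρ) and 1−ρ². Their ratio is (1+ρ)/2, so the reduction is (1−ρ)/2.

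| ρ | change | adjusted | reduction |
|---|---|---|---|
| 0.2 | 1.60 | 0.96 | 40% |
| 0.3 | 1.40 | 0.91 | 35% |
| 0.5 | 1.00 | 0.75 | 25% |
| 0.7 | 0.60 | 0.51 | 15% |
| 0.8 | 0.40 | 0.36 | 10% |

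At ρ = 0.5 the change score has variance 1.00, the same as comparing follow-up scores with no use of baseline at all. For such a contrast, 0.75 × 84 = 63 adjusted patients give the precision of 84 unadjusted ones.

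**4. Unequal SDs (assumption).** With s0/s1 = 0.8 and ρ = 0.5, the change variance is 0.64 + 1 − 0.80 = 0.84. The adjusted variance is 0.75, and 1 − 0.75/0.84 = 11%. With s0/s1 = 0.75 and ρ = 0.6 they are 0.6625 and 0.64, a reduction of about 3%.

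**5. The strata.** An age or gender effect that is constant over time is the same at t0 and t1 and cancels from the change. A simulation with 28 per arm, balanced strata and 4,000 runs per setting took ρ = 0.3, 0.5 and 0.7, with strata explaining 0, 5 or 10% of the variance. Adding age and gender changed the variance of the estimated contrast by less than 0.5% in every setting.

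In the baseline-adjusted model the strata do affect the reported standard error. If they explain a share b of PSQI variance, the residual variance falls from 1−ρ² to (1−b) − (ρ−b)²/(1−b). At ρ = 0.5 and b = 0.10 this is 0.9 − 0.16/0.9 = 0.722 against 0.75, about 4% less. At b = 0.20 it is 0.8 − 0.09/0.8 = 0.6875, about 8% less. These shares are assumptions.

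**The case against.** The strongest reply is that nothing in the plan is wrong. The mixed-design ANOVA is unbiased under randomisation, the sample size was computed for the same interaction test, and a condensed article may leave covariates to an analysis plan that is not shown. The first two points stand, and they limit this to an efficiency point. The third covers an unlisted covariate, but not the explicit decision to make baseline a level of the outcome.

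A second reply is that the size of the gain is uncertain, and that also stands. ρ = 0.5 is a planning input inferred from N = 84, not evidence about PSQI in these patients. Entry requires PSQI above 5, which may narrow the baseline spread. If the regression slope stays at 0.5 and the residual variance at 0.75 while s0 falls from 1 to 0.8, the change variance is 0.75 + (1−0.5)² × 0.64 = 0.91 and the gain drops from 25% to about 18%.

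Three stronger readings are tempting and are not supported:

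- **That leaving out the strata inflates the standard error of the planned contrast.** Effects constant over time cancel from it. Only an age or gender effect on the time trend would matter, and the document gives no sign of one.
- **That adjustment gains at every correlation below 1.** That needs equal SDs. In general the gain vanishes at s0 = ρ·s1.
- **That a specific rise in power can be quoted.** Converting f = 0.158 to a pairwise difference gives 4.5 × 0.158 = 0.71 SD. This holds only if SLA and control are identical and the LA effect is equal at t1 and t2, which the protocol does not say. Such a figure would also concern one unadjusted contrast at one visit, not the planned omnibus interaction test, whose power at 84 is 0.81.

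**Conclusion.** The point holds as a recommended improvement in precision. The stated primary model compares change scores where baseline adjustment is at least as precise, apart from the few degrees of freedom that the covariates use. On the assumption of equal SDs, the variance forgone for a pairwise contrast at one visit is 25% at ρ = 0.5, and 10% to 40% for ρ from 0.8 to 0.2. It is less if the baseline SD is below the follow-up SD. All of that gain comes from baseline PSQI. The case for including the strata is that the analysis should match the randomisation and that the reported standard error of the adjusted model should reflect it. A reader should not infer that the planned analysis is biased or invalid.

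**What to change.** Replace the primary model with one for PSQI at t1 and t2 containing group, visit, group × visit, baseline PSQI, baseline × visit, and the randomisation strata (age 18–40 or 41–60, and gender). A longitudinal model of all three visits with baseline means constrained equal across arms is an equivalent alternative.

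The text on comparisons must change with it. Once baseline is a covariate, the treatment effect is the difference between arms at each visit. The group × visit term only asks whether that difference changes from t1 to t2, so it should no longer decide whether pairwise comparisons are made.

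Use the same form, each outcome with its own baseline, for ISI, HAMD-17, 5-HT, cortisol and the actigraphy measures. Any power illustration added in support should state its assumed difference, SDs and ρ.

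The cost is a rewording of the statistical section. Baseline values, age and gender are already collected, and no visit, procedure or patient is added. The change should be fixed before any unblinded data are seen, so that the choice of covariates cannot appear data-driven.
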